## Abstract

**Objectives:**

For patients with a reduced left ventricular ejection fraction (LVEF) heart failure with reduced ejection fraction (HFrEF) and iron deficiency, administration of intravenous iron improves symptoms, exercise capacity and may in the following 12 months, reduce hospitalisations for heart failure. The Effectiveness of *I*nt*r*avenous ir*on* treat*m*ent versus standard care in p*a*tie*n*ts with heart failure and iron deficiency (IRONMAN) trial evaluated whether the benefits of intravenous iron persist in the longer term and impact on morbidity and mortality.

**Methods:**

IRONMAN is a prospective, randomised, open-label, blinded endpoint (PROBE) event-driven trial. Patients aged ≥18 years with HFrEF (LVEF ≤45%) and evidence of iron deficiency (ferritin <100 µg/L and/or TSAT <20%) were enrolled if they had either a current or recent hospitalisation for heart failure or elevated plasma concentrations of a natriuretic peptide. Participants were randomised to receive, or not to receive, intravenous ferric derisomaltose in addition to guideline-recommended therapy for HFrEF. Every 4 months, intravenous iron was administered if either ferritin was <100 µg/L or, provided ferritin was ≤400 µg/L, TSAT was <25%. The primary endpoint is a composite of total hospitalisations for heart failure and cardiovascular death. Hospitalisation and deaths due to infection are safety endpoints.

**Results:**

Trial recruitment was completed across 70 UK hospital sites in October 2021. Participants were followed until the end of March 2022. We plan to report the results by November 2022.

**Conclusions:**

IRONMAN will determine whether repeated doses of intravenous ferric derisomaltose are beneficial and safe for the long-term treatment of a broad range of patients with HFrEF and iron deficiency.

**Trial registration number:**

NCT02642562.

WHAT IS ALREADY KNOWN ON THIS TOPICIn patients with heart failure and reduced ejection fraction and associated iron deficiency, treatment with intravenous iron can improve symptoms, exercise capacity and may reduce hospitalisation for heart failure, in the following 12 months.WHAT THIS STUDY ADDSEffectiveness of *I*nt*r*avenous ir*on* treat*m*ent versus standard care in p*a*tie*n*ts with heart failure and iron deficiency (IRONMAN) is a randomised trial, powered to determine whether repeated doses of intravenous iron (ferric derisomaltose) are beneficial and safe in the long term in a broad range of patients with heart failure and reduced ejection fraction. The primary endpoint is a composite of total hospitalisations for heart failure and cardiovascular death.HOW THIS STUDY MIGHT AFFECT RESEARCH, PRACTICE OR POLICYThe results of IRONMAN will help to inform clinical practice and international guidelines with respect to the management of iron deficiency in patients with heart failure and reduced ejection fraction.

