### Sample size and statistical analysis

Sample size calculations based on recurrent event analyses are difficult (additional sample size calculations are given in online supplemental appendix 2). Conservatively, we based our calculations on a time to first event analysis in a Cox proportional hazards model. We expected to recruit half the participants during a hospitalisation. The anticipated first primary endpoint rate in the control group was 60% at 3 years. We estimated that 570 participants per group (yielding 631 first primary outcomes) would provide 80% power to detect an HR of 0.8 at the 5% significance level. Allowing for non-cardiovascular mortality and some withdrawals of consent for follow-up, we intended to recruit 650 patients per group.

10.1136/heartjnl-2022-321304.supp2Supplementary data

The Independent Data Monitoring Committee (IDMC) conducted interim analyses of the primary endpoint when approximately 50% and 70% of the target number of first primary endpoints had been reached, requiring p<0.001 to recommend early stopping.

The primary endpoint will be analysed by the method of Lin *et al*
9 including the randomised treatment group and recruitment context as covariates. The estimated rate ratio, 95% CI and p value will be reported, with accumulated events displayed using the method of Ghosh and Lin.^10^

Secondary endpoints will be analysed hierarchically in the order shown in box 2, if the primary analysis is significant at the 5% level. Endpoints in the list will continue to be tested until one fails to reach 5% significance. Power calculations have been carried out for the first four secondary endpoints (online supplemental appendix 2).

Secondary endpoints involving recurrent events will be analysed as for the primary endpoint. Time to first event outcomes will be analysed using Cox proportional hazards models including treatment effect and recruitment context, with the treatment effect HR and 95% CIs estimated with associated p values using the Wald statistic and treatment groups compared graphically using cumulative incidence functions.

QoL scores and 6 min walk tests results at 4 and 20 months will be compared between randomised treatment groups using analysis of covariance, with treatment group and stratification variable as covariates.

Subgroup analyses will be carried out for the primary endpoint, analysed as a recurrent event and then separately as time-to-first event.

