### Modifications to sample size

In practice, we recruited mainly outpatients who had a lower rate of events; recruitment was slower than expected, especially during the COVID-19 pandemic, which also may have reduced cardiovascular admissions, resulting in a lower event rate for the primary endpoint. This, in combination with likely patient and investigator fatigue, led the Trial Steering Committee (TSC) to revise the power calculation for the trial. Assuming an HR of 0.75, as in AFFIRM-AHF trial,^11^ we calculated that 379 first primary endpoints would now provide 80% power at the 5% significance level.

Analyses based on patients randomised until the end of March 2020 with a censoring date of 30 September 2020 will be carried out to assess the impact of the COVID-19 pandemic on the results.

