### Safety of intravenous iron

There are theoretical risks associated with repeated intravenous iron dosing. Labile (free) iron can result in the generation of reactive oxygen species, which could lead onto oxidative stress and cell damage.^17^ A meta-analysis of studies across a broad range of conditions found that intravenous iron was associated with an increased risk of infection (rate ratio (RR) 1.17; 95% CI 1.04 to 1.31).^8^ This was not confirmed across heart failure studies. Most studies did not define infection a priori, and the authors note potential bias. A trial investigating liberal versus conservative dosing with intravenous iron sucrose in haemodialysis patients found no difference in infection rates.^18^ IRONMAN, with death and hospitalisation due to infection as safety endpoints, will help clarify the long-term safety of intravenous iron in patients with heart failure.

Two other ongoing randomised outcome trials of intravenous ferric carboxymaltose include patients with HFrEF: HEART-FID^19^ and FAIR-HF 2 (NCT03036462). Important differences (see online supplemental appendix 5) in trial designs should help establish which patients with heart failure get the most benefit from intravenous iron and inform the current disparity among international guidelines.^20–22^

10.1136/heartjnl-2022-321304.supp5Supplementary data

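### The summary says the trial is powered to determine safety, but every power calculation the article describes is for efficacy, and power against the infection excess it cites is low at plausible event counts

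*Protocol article*

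**What the plan says.** The key-messages box that follows the abstract (under the trial registration number, in the part on what the study adds) describes the trial as "powered to determine whether repeated doses of intravenous iron (ferric derisomaltose) are beneficial and safe in the long term". The abstract's Conclusions make the matching promise without mentioning power: "IRONMAN will determine whether repeated doses of intravenous ferric derisomaltose are beneficial and safe".

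The section on sample size and statistical analysis states that "570 participants per group (yielding 631 first primary outcomes) would provide 80% power to detect an HR of 0.8 at the 5% significance level", with a recruitment target given as "we intended to recruit 650 patients per group". The section on modifications to sample size replaces the effect size ("Assuming an HR of 0.75, as in AFFIRM-AHF trial") and arrives at 379 first primary endpoints for 80% power. Beyond the primary endpoint, "Power calculations have been carried out for the first four secondary endpoints". In Box 2 those four are recurrent heart failure hospitalisation, first cardiovascular hospitalisation, cardiovascular death or heart failure hospitalisation as a first event, and the overall Minnesota score at 4 months.

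The two safety endpoints, death due to infection and hospitalisation primarily for infection, close Box 2 after twenty efficacy endpoints. The article attaches no expected count, margin or power to either. The section on safety of intravenous iron reports a meta-analysis in which "intravenous iron was associated with an increased risk of infection (rate ratio (RR) 1.17; 95% CI 1.04 to 1.31". It adds that the pooled studies covered many conditions and that heart failure studies did not bear the finding out. It then says only that the trial will contribute to clarifying long-term safety.

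**The concern.** To say that a trial is powered for a question is a quantitative claim. It means that a named effect would be detected, or excluded, with a stated probability. In the key-messages box the word governs safety as well as benefit, yet the article describes no calculation that supports the safety half.

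What is at stake is how the infection result is read. The Introduction wants the theoretical risks, infection among them, confirmed or refuted by clinical evidence, and the key-messages box expects the results to inform guidelines. If the trial is on record as powered for safety, a non-significant infection comparison may be taken as evidence of safety while its confidence interval still includes an excess of the size that the article cites.

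**Working it through.** **Inputs from the article.** Equal allocation; 5% significance level, taken as two-sided because that reproduces the stated figures; 80% power; hazard ratio 0.8 with 631 first events, later 0.75 with 379; 650 per group, so 1,300 in total; infection ratio 1.17. The article gives no infection rate.

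**Step 1: reproduce the plan's own figures.** Schoenfeld's formula for equal groups is d = 4(1.960 + 0.842)² / (ln HR)², with a numerator of about 31.40.

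- HR 0.80: 31.40 / (0.2231)² gives 631 after rounding up. Stated: 631.
- HR 0.75: 31.40 / (0.2877)² = 379.35. Stated: 379, which gives 80.0% power.

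Both agree, so the same formula is a fair yardstick for infection.

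**Step 2: apply it to a ratio of 1.17.** ln 1.17 = 0.1570, so d = 31.40 / (0.1570)² = 1,274 first infection events. As a share of the planned sample, 1,274 / 1,300 = 98%.

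The chance of excluding 1.17 when the true ratio is 1 is Φ(ln 1.17 × √d / 2 − 1.96). This is the same expression as the power to detect 1.17, so the requirement is again 1,274.

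**Step 3: precision.** At an observed ratio of 1.00 the upper 95% limit is exp(3.92 / √d). It falls below 1.17 only when d exceeds (3.92 / 0.1570)² ≈ 623, so from 624 events.

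**Step 4: a range of event counts.** The shares of 10%, 20% and 30% of 1,300 are assumptions. The largest observed ratio that excludes 1.17 is 1.17 / exp(3.92 / √d).

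| First infection events | Power at 1.17 (= chance of excluding it if true ratio is 1) | Upper 95% limit at observed 1.00 | Observed ratio needed to exclude 1.17 |
|---|---|---|---|
| 130 (10%) | 14% | 1.41 | about 0.83 or lower |
| 260 (20%) | 24% | 1.28 | about 0.92 or lower |
| 300 (23%) | 27% | 1.25 | about 0.93 or lower |
| 390 (30%) | 34% | 1.22 | about 0.96 or lower |

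With 300 events the smallest ratio detectable at 80% power is 1.38.

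**Step 5: if iron lowers infection.** With 300 events the chance of excluding 1.17 is 62% if the true ratio is 0.9 and 91% if it is 0.8.

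**Step 6: sensitivity to the measure.** If 1.17 is treated as a ratio of two proportions with 650 per arm, power is 17%, 32% and 50% at control risks of 10%, 20% and 30%. It is 70% at a control risk of 40% and 87% at 50%, so 80% is reached only between those two values. The requirement is milder on this reading, but power is still at most about one half over the assumed range.

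**The case against.** The strongest reply is that this is loose summary wording and nothing more. The body of the article speaks of investigating, assessing and clarifying safety; no endpoint, analysis or decision rule rests on the sentence; and the Conclusions do not mention power. This stands as a limit on the weight of the point. It does not make the sentence correct.

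The 1.17 benchmark can also be challenged. It comes from a broad range of conditions and was not confirmed in heart failure. The article notes potential bias and that most of the studies had not defined infection in advance. It concerns infection in general, whereas the trial counts infection hospitalisations and infection deaths, and the article never sets it as a margin. All of that stands. It is used here only because it is the one infection effect size the article offers.

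The calculation counts first events, while Box 2 does not restrict infection hospitalisation to the first. Recurrent events would add information, though overdispersion would offset part of the gain.

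Three stronger readings may tempt a reader, and the article supports none of them:

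- *The trial cannot exclude 1.17.* It can, if the observed ratio is far enough below 1 (steps 4 and 5).
- *The revised target of 379 limits the safety data.* That figure counts first primary efficacy events; it does not cap infections, and the article states no cut in recruitment with it.
- *No power was ever set for safety.* Additional calculations are in supplemental appendix 2, which is not shown. One can say only that the article describes none.

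**Conclusion.** The point holds as an overclaim in the summary. The article calls the trial powered to determine safety, describes power only for efficacy, and is more modest in its own safety section.

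Against the infection excess it cites, 80% power on the sponsor's own method would need about 1,274 first events, or 98% of planned participants. That figure depends only on the stated error rates, equal allocation and treating 1.17 as a hazard ratio. The power of 14–34% and the upper limits of 1.41 to 1.22 also rest on an assumed 10–30% of participants having a first infection hospitalisation. A higher rate, or treating 1.17 as a ratio of proportions, would improve the figures.

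No number in the article is wrong, and the primary analysis is unaffected. The consequence is confined to what a null infection result may be said to show.

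**What to change.** 1. In the key-messages box, separate the power claim from safety, for example: powered for efficacy; infection risk will be estimated with a 95% CI.
2. Bring the abstract's Conclusions into line with the more modest statement in the section on safety of intravenous iron.
3. State that a non-significant infection result will be reported with its confidence interval and the increase that the interval does not exclude, and not as showing safety. The article says the statistical analysis plan will be finalised before database lock, so this can still be recorded there.

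A named safety margin is not needed for this repair. The cost is wording only: no change to design, data or primary analysis, and a less favourable stated claim.

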## Introduction

Iron is an essential component of haemoglobin, myoglobin, the mitochondrial electron transport chain and many enzymes. Patients with heart failure, with or without reduced left ventricular ejection fraction (LVEF), often have anaemia, and this will usually be due to iron deficiency.^1–3^ However, iron deficiency is also common in patients without anaemia.^1–3^ Iron deficiency, with or without anaemia, is associated with more severe symptoms and a worse prognosis.^1–3^

Placebo-controlled studies have demonstrated that intravenous administration of ferric carboxymaltose in ambulatory patients with heart failure and reduced LVEF (HFrEF) improves exercise capacity, symptoms and quality of life (QoL).^4 5^ Iron deficiency was defined as serum ferritin <100 µg/L, or between 100 and 300 µg/L if transferrin saturation (TSAT) <20%. In both studies, the respective primary endpoint was evaluated at 24 weeks. A trial of predischarge intravenous ferric carboxymaltose to patients who had been hospitalised with acute heart failure (AFFIRM-AHF)) suggested that treatment to 6 months might reduce the risk of recurrent hospitalisations for heart failure but not cardiovascular mortality when assessed at 52 weeks, although the effect on its primary endpoint, a composite of recurrent hospitalisations for heart failure and cardiovascular death, was of borderline significance.^6^ A meta-analysis of seven randomised trials of patients with HFrEF and iron deficiency found that intravenous iron reduced the risk of hospitalisation for heart failure but was unable to demonstrate a reduction in cardiovascular mortality.^7^

Major gaps in our knowledge remain, including the long-term benefits and safety of repeated administration of intravenous iron. Although the rationale for benefit is clear, bypassing evolutionary systems that have evolved to prevent iron overload also poses theoretical risks, including increased oxidative stress, mitochondrial damage and infection.^8^ These theoretical risks should be confirmed or refuted by clinical evidence. The Effectiveness of *I*nt*r*avenous ir*on* treat*m*ent versus standard care in p*a*tie*n*ts with heart failure and iron deficiency (IRONMAN) trial was designed and conducted in the UK to investigate the benefits and safety of repeated doses of intravenous ferric derisomaltose over an extended period, which should help inform clinical practice and international guidelines.

## Trial design

IRONMAN is a prospective, randomised open-label, blinded endpoint (PROBE) event-driven trial designed to assess the efficacy and safety of intravenous ferric derisomaltose in symptomatic patients with HFrEF and iron deficiency. The endpoints committee adjudicating events are kept blinded to assigned treatment.

Patients aged ≥18 years with new or established symptomatic HFrEF (LVEF ≤45% within the preceding 24 months) were invited to participate. Iron deficiency was defined as serum ferritin <100 µg/L and/or TSAT <20%. In addition, patients either had to have a current or recent (<6 months) admission for heart failure (including daycare intravenous diuretics) or have increased plasma concentrations of a natriuretic peptide (NT-proBNP >250 ng/L in sinus rhythm or >1000 ng/L in atrial fibrillation or equivalent for BNP, box 1).

Box 1Inclusion/exclusion criteriaInclusion criteriaAge ≥18 yearsLeft ventricular ejection fraction (LVEF) ≤45% within the last 2 years using any conventional imaging modality (most recent assessment)NYHA class II–IVIron deficient – defined as transferrin saturation (TSAT) <20% and/or ferritin <100 ug/L.Evidence of being in a higher risk heart failure group:Current or recent (within 6 months) hospitalisation for heart failure.Outpatients with NT-proBNP >250 ng/L in sinus rhythm or >1000 ng/L in atrial fibrillation (or BNP >75 pg/mL or 300 pg/mL, respectively).Able and willing to provide informed consent.Exclusion criteriaHaemoglobin <9 g/dL or 13 g/dL in women or >14g/dL in men.Ferritin >400ug/L.eGFR <15 mL/min/1.73 m^2^ (MDRD/CKD-EPI).Already planned to receive intravenous iron.Likely to need or already receiving erythropoiesis-stimulating agents.Blood transfusion in the previous 3 months or active clinically relevant bleeding in the investigator’s opinion or known or suspected gastrointestinal malignancy.Planned cardiac surgery or revascularisation.Any major vascular event in the previous 3 months, including type 1 myocardial infarction, cerebrovascular accident, major cardiovascular surgery or percutaneous coronary intervention.Awaiting or treated by cardiac transplantation or left ventricular assist device.Active infection (if the patient has significant ongoing infection, recruitment should be postponed until it has resolved or been controlled).Any disease other than heart failure with a life expectancy of <2 years.Pregnancy, breast feeding or childbearing potential in the absence of effective contraception.Contraindication to intravenous iron according to contemporary Summary of Product Characteristics including hypersensitivity to Monofer ® or any of its excipients; known serious hypersensitivity to other parenteral iron products; anaemia due to causes other than iron deficiency (eg, haemolytic anaemia); iron overload or disturbances in utilisation of iron (eg, haemochromatosis and haemosiderosis); and decompensated liver disease.Participation in another intervention study involving a drug or device within the past 90 days (coenrolment in observational studies is permitted).BNP, B-type natriuretic peptide; CKD-EPI, Chronic Kidney Disease Epidemiology Collaboration; eGFR, estimated glomerular filtration rate; LVEF, left ventricular ejection fraction; MDRD, modification of diet in renal disease; NYHA, New York Heart Association; NT-proBNP, N-terminal pro B-type natriuretic peptide.

Patients were excluded if they had high ferritin (>400 µg/L), a haemoglobin <9.0 g/dL or an estimated glomerular filtration rate (eGFR) <15 mL/min/1.73 m^2^. Iron deficiency is less common when haemoglobin is more than 1 g/dL above the WHO definition of anaemia. Accordingly, to reduce screen failures, men with a haemoglobin >14 g/dL and women with values >13 g/dL were excluded. A detailed list of inclusion and exclusion criteria is shown in box 1.

## Trial plan

An overview of the trial is shown in figure 1 and schedule of assessments in the online online supplemental appendix 1. Written informed consent was obtained for participation in the trial, with additional optional consent for follow-up of electronic medical records (from 1 year prior to consent until 10 years after trial completion) and to provide blood samples at baseline, 4 and 20 months for subsequent biomarker analysis.

10.1136/heartjnl-2022-321304.supp1Supplementary data

**Figure 1 F1:**
[figure not shown]
Overview of the Ironman trial: visit schedule and procedures. *See box 1 for full list of inclusion and exclusion criteria. CRP, C reactive protein; EGFR, estimated glomerular filtration rate; SAE, serious adverse event.

### Randomisation

Consenting and eligible patients were randomised with equal probability to the two treatment arms, stratifying by recruitment context (in hospital, recently discharged or ambulatory with elevated natriuretic peptide) and trial site, using a web-based system based on randomised, permuted blocks of variable size.

### Treatment

Participants assigned to intravenous iron were administered ferric derisomaltose by infusion at a dose determined by haemoglobin value and body weight (table 1). At each visit, investigators were encouraged to optimise heart failure therapy for both groups, according to contemporary guidelines.

**Table 1 T1:** Intravenous ferric derisomaltose infusion dose regimen

Haemoglobin	Body weight <50 kg*	Body weight 50– <70 kg	Body weight ≥70 kg
≥10 g/dL	20 mg/kg	1000 mg	20 mg/kg up to a maximum of 1500 mg
<10 g/dL	20 mg/kg	20 mg/kg	20 mg/kg up to a maximum of 2000 mg

The dosing table permits an estimation of iron need and utilises a pragmatic approach that takes into consideration a patient’s weight and haemoglobin concentration. Doses up to and including 1000 mg – infused over >15 min. Doses exceeding 1000 mg – infused over 30 min or more.

*At trial design guidance for calculating iron need for this patient group was limited; therefore, a pragmatic administration approach was taken to ensure patients did not receive higher than the maximum licenced dose.

A key goal was to try and ensure that those assigned to intravenous iron were kept iron replete, with redosing with intravenous ferric derisomaltose at the 4-week review and every 4 months after randomisation if either the ferritin was <100 µg/L or, provided ferritin was ≤400 µg/L, TSAT was <25%. If iron deficiency recurred, investigators were encouraged to consider further investigations for potential sources of blood loss. Oral iron supplementation was permitted at the discretion of the investigator in the standard care arm. Any use of non-trial iron supplements was recorded.

The data collected at each timepoint varied, with more in-depth assessment taking place at randomisation, 4 and 20 months (figure 1, online supplemental appendix 1). This included detailed laboratory analysis (local laboratories), 6 min walk test (where possible) and assessments of QoL (Minnesota Living With Heart Failure and EQ-5D).

